**Satisfaction and sense of safety of participating health professionals in the care of pregnant women and newborns**		
1–5	Telemedicine contacts with the university hospital - helpful or not and reasons why	telemedicine questionnaire survey
	Can the questions be answered via telemedicine	telemedicine questionnaire survey
	Job satisfaction	questionnaire survey, self-developed items based on COPSOQ (Kristensen et al., 2005; German version Nübling et al., 2006)
	Sense of safety in neonatal care	questionnaire survey, self-developed case vignettes
	When / why do health professionals in the respective participating facilities use the intervention bundle and when / why not?	questionnaire survey, self-developed items; qualitative interviews
	What has changed as a result of the intervention bundle - both positively and negatively?	qualitative interviews
	Reasons for (dis)satisfaction	qualitative interviews
	Reasons for feeling safe	qualitative interviews
**Satisfaction with medical care and resilience of patients and families (questionnaire survey 3 months after study inclusion for IB#1 and 3 months after calculated delivery date for IB#2–5; qualitative interviews with selected individuals)**		
1–5	Satisfaction with care	self-developed items
	Reasons for (dis)satisfaction	qualitative interviews
	Resilience	BRS - Brief Resilience Scale (Chmitorz et al., 2018)
	Reasons for resilience	qualitative interviews
	Quality of life	WHOQOL-BREF (The WHOQOL Group, 1998)
	Depressive, anxiety and stress symptoms	DASS-P: Depression Anxiety Stress Scale for the Peripartal Period (Martini et al., 2009)
	Reasons for use of individual services	qualitative interviews
**Economic impact**		
1	Number of duplicate clinic presentations: Referrals to the Perinatal Center of the University Hospital	project database
	Required travel distances to the medical examination at the Perinatal Center of the University Hospital: travel distance from the patient’s home to the university hospital and back	project database
	Inpatient costs of mother (for 6 months before birth)	SHI routine data of the participating health insurance company
	Number of transfers of the mother	SHI routine data of the participating health insurance company
	Costs of transports between hospitals	SHI routine data of the participating health insurance company
	Duration of inpatient stays of the mother (for 6 months before birth)	SHI routine data of the participating health insurance company
	Outpatient costs for gynecological specialists and prenatal physicians	SHI routine data of the participating health insurance company
	Periods of inability to work during pregnancy	SHI routine data of the participating health insurance company
	Expenditures during the inpatient stay of the mother (measured by OPS codes)	SHI routine data of the participating health insurance company
2–5	Inpatient costs of the child (up to 6 months after birth)	SHI routine data of the participating health insurance company
	Number of transfers of the child related to the inpatient stay at birth	SHI routine data of the participating health insurance company
	Costs of transports between hospitals	SHI routine data of the participating health insurance company
	Duration of ventilation time [hours] of the child	SHI routine data of the participating health insurance company
	Number of inpatient stays of the child (for the 6 months after first discharge after birth)	SHI routine data of the participating health insurance company
	Expenditures for the child during the inpatient stay (measured by OPS codes)	SHI routine data of the participating health insurance company

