### Eligibility criteria

All patients or newborns meeting the following criteria will be included:

IB#1: Pregnant women with a disorder affecting fetal health (e.g. gestational diabetes) or with a suspicion of a serious disease of the fetus who are cared for on an outpatient basis by a participating prenatal obstetrician,IB#2: Newborns cared for in the delivery room or admitted as inpatients who required resuscitation or intensive care at the participating hospital,IB#3: Newborns admitted as inpatients who receive antibiotic therapy at the participating hospital and/or have a positive microbiologic screening result,IB#4: Premature or sick newborn receiving inpatient care at a participating hospital or the PC-UKD with a suspected need for transfer to the PC-UKD or indication for transfer back close to home,IB#5: Families of newborns hospitalized at a participating hospital for more than 5 days.

The secondary study population consists of outpatient obstetricians and health professionals at the hospitals using IB.

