### Intervention bundles (IB) of the health care network “SAFE BIRTH” (HCNSB)

#### Intervention bundle #1: Multi-professional, inter-disciplinary prenatal care plan

In Germany, midwives and outpatient obstetricians care for pregnant women. In the event of any abnormalities, pregnant women are examined by a specialist for prenatal diagnostics. If the suspicion of a fetal abnormality or maternal risk is confirmed, prompt multi-disciplinary and inter-professional planning of further steps is necessary. Currently, the development of an individual care plan is usually done in a specialized perinatal center. This current process is associated with lengthy waiting times and increased health care costs [3]. Psycho-social aspects are often not adequately addressed [3].

IB#1 is aimed at all pregnant women with fetal or maternal abnormalities requiring control at the PC-UKD and consists of the following measures:

The **prenatal tele-consultation** enables the outpatient obstetrician to have an immediate virtual consultation with the expert of the PC-UKD while the pregnant woman is still present.In the **prenatal jour-fixe**, recorded findings are discussed in the virtual room, without the participation of the pregnant woman.Subsequently, the **prenatal care plan** is determined, if necessary with the involvement of other disciplines.In addition, the psycho-social team of the PC-UKD contacts the pregnant woman by telephone, thus ensuring prompt **psycho-social counseling** tailored to the individual characteristics.A virtual **feto-neonatal board meeting** serves to review and adapt the prenatal care plan to current findings during care.

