### Assignment of interventions

The decision whether a newborn/patient is assigned to the intervention or control group depends on the time of inclusion. If the recruiting facility is in the control phase, the patient or newborn is assigned to the control group, otherwise to the intervention group. There is no blinding. The order in which the recruiting facilities enter the intervention phase is randomized. Figure 3 illustrates the allocation of clinics and prenatal medical outpatient offices to the intervention time points defined within the 30-month observation period.

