### Data analysis

As part of the confirmatory analysis, we examine the effectiveness of the intervention bundles using the IB-specific primary outcomes (Chap. 2). A separate logistic multilevel regression model is estimated for each primary outcome, which contains the intervention status (control or intervention phase) of the respective patient or newborn facility as an explanatory variable. The coefficient of this explanatory variable represents the intervention effect. To account for the clustered structure and the possible correlation of patient outcomes within the institutions, all models contain a random intercept at the institutional level [16]. The estimation results support the respective primary hypothesis if the estimated intervention effect is positive and statistically significant. Significance is tested using a two-tailed test with a significance level of 5%. To control for the inflation of the Type 1 error in our setting where we conduct multiple tests, Holm-Bonfferoni correction is used [17].

For testing of hypothesis 1, we compare data for the control and intervention group by analyzing frequencies and mean values, confidence intervals and conducting adjusted regression models.

The qualitative semi-structured interviews will be audio recorded and transcribed verbatim. The transcripts will be analyzed content-analytical using inductive and deductive coding.

Secondary hypothesis 2 (health economic evaluation) will be assessed by analyzing statutory health insurance routine data for each patient case. For each intervention bundle, we sum up the inpatient costs and costs for transfers of the individual patients, and, if mother and child are insured by AOK Plus, costs associated to their newborns in the context of their birth and costs in the 6 months following birth. In the next step, we compare average costs between the intervention and control phase cases and determine the difference in costs. Additionally, we compare the following aspects between the control and intervention group: patient transfers; length of inpatient stays; risks, complications and expenses during the inpatient stay; and more frequent clinic presentations. Expenses for patients and the medical staff involved will be included in the analysis (Table 1, last line).

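### IB#1 maternal inpatient cost and stay outcomes, counted over 6 months back from birth, can include care given before inclusion; this mainly costs precision and can be removed by covariate adjustment

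*Protocol article*

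**What the plan says.** Table 1 of the protocol article, under Economic impact, lists nine rows for IB#1. Two carry a window that runs backward from delivery: "Inpatient costs of mother (for 6 months before birth" and "Duration of inpatient stays of the mother (for 6 months before birth", each closing its bracket there. No other condition is attached.

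Under Eligibility criteria, IB#1 takes in "Pregnant women with a disorder affecting fetal health (e.g. gestational diabetes) or with a suspicion of a serious disease of the fetus", provided a participating prenatal obstetrician looks after them as outpatients. No gestational age is given. Under Assignment of interventions, "The decision whether a newborn/patient is assigned to the intervention or control group depends on the time of inclusion". The first IB#1 component is a teleconsultation that "enables the outpatient obstetrician to have an immediate virtual consultation with the expert of the PC-UKD while the pregnant woman is still present".

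For the economic hypothesis, the Data analysis section says "we sum up the inpatient costs and costs for transfers of the individual patients". It adds newborn costs where mother and child are both insured with the participating fund, and then "we compare average costs between the intervention and control phase cases and determine the difference in costs".

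**The concern.** Two clocks are in use. Exposure starts at inclusion, while maternal cost is counted back from birth, and nothing in the article links the two. For a woman included in mid or late pregnancy, part of the 6 months has passed before she meets the criteria. IB#1 cannot have changed an admission in that part. For a woman included soon after her office crosses over, that part was also delivered under control conditions, although she is counted as an intervention case.

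At stake is secondary hypothesis 2 (cost-effectiveness from the insurer's perspective) for IB#1. Cost that the intervention cannot touch adds variance to the phase contrast. It also dilutes any effect expressed as a ratio or percentage, because the same untouched amount sits in both averages. No primary outcome and no sample-size figure depends on these rows.

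**Working it through.** The plan states no figure for this point, so there is none to reproduce. The check has four steps.

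**1. Does the window reach before inclusion?** Six months is 365.25 / 2 / 7 = 26.1 weeks. The window opens at birth week − 26.1. The pre-inclusion share of the window is 1 − (birth week − inclusion week) / 26.1, with a floor of zero. The document gives no gestational ages at inclusion or birth, so the weeks below are assumptions.

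| Birth week | Window opens | Inclusion week | Pre-inclusion share |
|---|---|---|---|
| 40 | 13.9 | 20 | 23% |
| 40 | 13.9 | 24 | 39% |
| 40 | 13.9 | 28 | 54% |
| 40 | 13.9 | 32 | 69% |
| 34 | 7.9 | 20 | 46% |
| 34 | 7.9 | 28 | 77% |

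The reverse case is small. With inclusion at week 12 and birth at week 40, 40 − 12 − 26.1 = 1.9 weeks after inclusion fall outside the window.

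**2. Does the described analysis remove it?** The Data analysis section neither limits the summed costs to the time after inclusion nor names earlier cost as a covariate. The Abstract mentions multilevel regression with confounder adjustment and gives socioeconomic status, age and residence as examples. Neither prior cost nor gestational age at inclusion is among them.

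**3. What could it cost in precision?** Let *s* be the share of the variance of the mother's windowed cost that arises before inclusion, assumed independent of later cost. The standard error is then larger by a factor 1/√(1 − *s*). If a comparison would have 80% power at two-sided 5% without this noise, its power with the noise is Φ((1.960 + 0.842)·√(1 − *s*) − 1.960).

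| Assumed *s* | SE factor | Power instead of 80% |
|---|---|---|
| 10% | 1.054 | 76% |
| 25% | 1.155 | 68% |
| 50% | 1.414 | 51% |

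The values of *s* are illustrative. They are not the time shares from step 1, and the 80% is a reference point, since the article claims no power for this outcome.

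**4. Must the window be replaced?** Write the window total as T = P + A, where P is in-window cost before inclusion and A is in-window cost after it. Let Z be phase and G gestational age at inclusion. If T = α + βZ + γP + δG + error, subtracting P from both sides gives A = α + βZ + (γ − 1)P + δG + error. The intervention effect β and its standard error are the same. In a linear model, adjusting for P therefore removes the pre-inclusion noise with the stated window kept as the outcome.

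**The case against.** A window anchored at birth is a defensible choice. It has equal length for every woman, and in an unblinded trial it does not depend on when an office registers her. Counting from inclusion to birth has neither property. Its length is set partly by the timing of birth, which gestational age at inclusion does not fully account for, so an early birth after a complicated pregnancy can look cheap. This stands, and it is why the window should not simply be replaced.

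A reader might also infer three stronger things that the document does not support.

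- **That the comparison is of raw averages.** The article speaks of average costs but does not call them unadjusted, and the Abstract points to adjusted models. Further covariates may be specified in an analysis plan that is not shown. What remains is that the window itself is fixed in the article and no remedy for it is described.
- **That the cost difference is biased.** If pre-inclusion cost has the same expectation in both phases, the absolute mean difference is unbiased. Nothing in the document shows otherwise.
- **That the loss is large for hypothesis 2 as a whole.** Treating a 54% time share as a variance share would give 1/√0.46 = 1.47, a standard error 47% larger. That needs variance to accrue evenly over the window. If inpatient cost concentrates near birth, the loss is much smaller. It would also apply only to the mother's antenatal component, whereas the planned sum includes transfer costs and, for some pairs, newborn costs. The formula treats women as independent, and variation between the five offices and over time would not shrink in the same way.

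**Conclusion.** The point holds as a minor one. The two maternal outcomes can include care from before inclusion, which IB#1 cannot influence, and the article describes nothing that takes it out. The main effect is a loss of precision in the mother's antenatal component of secondary hypothesis 2, with dilution if the result is reported as a relative difference.

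The size cannot be derived from the document. It depends on gestational age at inclusion and on how inpatient cost is spread over the 6 months, and neither is given. The range of about 5% to 41% in the standard error rests on assumed variance shares of 10% to 50% and on independence of earlier and later cost. The weeks lost for women included very early are a side issue.

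**What to change.** Keep the 6-month window as the outcome and split it at the inclusion date. Compare phases in a regression that adjusts for the mother's in-window inpatient costs before inclusion (days, for the length-of-stay outcome) and for gestational age at inclusion. Report costs from inclusion to birth as a sensitivity analysis; this also picks up the weeks that the window drops for women included early.

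Two cautions belong in the wording. The equivalence in step 4 holds for a linear model; with a log-link cost model the choice between window total and post-inclusion part matters and should be stated. Adjustment also does not make time after inclusion equal between women, so the planned difference in average cost over the full window should still be reported beside the adjusted one.

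The cost is a little more analysis work. It uses dated claims that are already planned for, linked to the inclusion date, and needs no new data collection. It can be settled before the analysis starts.

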**Expenditures for the novel form of care**		
1–5	Type, duration, number and type of participants are recorded for each measure	project database

### Sample size and recruitment

The first patient/newborn was included on 29 January 2023. The inclusion of the last patients and newborns will take place by 30 June 2025 at the latest.

We estimated a separate multilevel logistic regression model for each primary outcome. Across all IB, 1,417 pregnant women or newborns need to be included in the control group and 1,541 in the intervention group. Calculations are based on consortium leadership surveys from April 2020 to April 2021 among participating health professionals [3] and yielded power above 80% for small to medium intervention effects for all five hypothesis tests. The intervention effect results from the change in the probability of achieving the target between the intervention and control phases. A drop-out rate of 10% was calculated.

Participating prenatal medical outpatient offices and hospitals recruit the study participants.

### Assignment of interventions

The decision whether a newborn/patient is assigned to the intervention or control group depends on the time of inclusion. If the recruiting facility is in the control phase, the patient or newborn is assigned to the control group, otherwise to the intervention group. There is no blinding. The order in which the recruiting facilities enter the intervention phase is randomized. Figure 3 illustrates the allocation of clinics and prenatal medical outpatient offices to the intervention time points defined within the 30-month observation period.

**Fig. 3 Fig3:**
[figure not shown]
Result of the sequence generation for clinics and outpatient offices

### Data collection and management

The primary and secondary outcomes are collected via three prospective primary data sources and one secondary data source (Fig. 4). Data source (1) is a project database (REDCap), in which patient cases and process data are documented. For instance, data on the health status of the pregnant woman and the newborn, referrals and interventions carried out are recorded, and process data on the type, duration, number and type of participants per intervention. Data source (2) is composed of two questionnaire surveys. Patients or parents and guardians of newborns are given access to an online questionnaire 3 months after study inclusion, which measures their satisfaction with care (self-developed), resilience (BRS - brief resilience scale [9]), quality of life (WHOQOL-BREF [10], and psychosocial distress (DASS-P - Depression Anxiety Stress Scale for the Perinatal Period [11]). The second questionnaire survey is designed for health professionals at participating hospitals caring for newborns. They will receive a paper questionnaire at 3 measurement points, which measures their sense of safety in the care of newborns by means of self-developed case vignettes and job satisfaction (based on COPSOQ (Copenhagen Psychosocial Questionnaire) [12], German version [13]) in the course of the project. Semi-structured individual telephone interviews will be the data source (3). Qualitative interviews will be conducted with 5 outpatient obstetricians, 12 inpatient health professionals and 12 patients and guardians of newborns about barriers to the use of IB and reasons for the quantitatively measured outcomes. Routine SHI data of the participating health insurance companies will be the data source (4). Among other things, referrals, transports and transfers, complications, inpatient length of stay, travel distances and costs will be used as the data basis for the evaluation.

**Fig. 4 Fig4:**
[figure not shown]
Data sources

The German association “Das Frühgeborene Kind e. V.” (English: “The preterm child”, a registered association to support preterm children and their parents by education, information, offers of help, research and political participation) was involved in the development of the questionnaire set for patients and guardians. The representatives of the association received a proposal for the outcome dimensions recorded in the questionnaire set and had the opportunity to add additional outcomes. At the same time, they received a draft questionnaire with a request for critical review and the opportunity to add further ideas. As the feedback from the representatives was transferred to the questionnaire set and to the web application SoSci Survey [14], three members of the study council of the association tested the questionnaire set for comprehensibility and feasibility. Based on these pre-tests, we were able to revise unclear questions. In addition, we added justifications for the use of standardized instruments to the questionnaire to increase compliance among respondents.

Qualitative sampling plans will be developed for the selection of heterogeneous interviewees. In terms of a mixed methods design, the results from the quantitative questionnaire survey also serve this selection. If possible, the interviewees should be heterogeneous regarding their satisfaction and sense of safety in order to explore why some individuals benefit more and others less from the intervention and whether the effects are due to the intervention or also to other accompanying circumstances. This is an explanatory sequential design [15] because the qualitative survey builds on the quantitative survey.

Data management procedures are fixed in a data protection concept. Details of data management procedures can be requested from the authors.

### Data analysis

As part of the confirmatory analysis, we examine the effectiveness of the intervention bundles using the IB-specific primary outcomes (Chap. 2). A separate logistic multilevel regression model is estimated for each primary outcome, which contains the intervention status (control or intervention phase) of the respective patient or newborn facility as an explanatory variable. The coefficient of this explanatory variable represents the intervention effect. To account for the clustered structure and the possible correlation of patient outcomes within the institutions, all models contain a random intercept at the institutional level [16]. The estimation results support the respective primary hypothesis if the estimated intervention effect is positive and statistically significant. Significance is tested using a two-tailed test with a significance level of 5%. To control for the inflation of the Type 1 error in our setting where we conduct multiple tests, Holm-Bonfferoni correction is used [17].

For testing of hypothesis 1, we compare data for the control and intervention group by analyzing frequencies and mean values, confidence intervals and conducting adjusted regression models.

The qualitative semi-structured interviews will be audio recorded and transcribed verbatim. The transcripts will be analyzed content-analytical using inductive and deductive coding.

Secondary hypothesis 2 (health economic evaluation) will be assessed by analyzing statutory health insurance routine data for each patient case. For each intervention bundle, we sum up the inpatient costs and costs for transfers of the individual patients, and, if mother and child are insured by AOK Plus, costs associated to their newborns in the context of their birth and costs in the 6 months following birth. In the next step, we compare average costs between the intervention and control phase cases and determine the difference in costs. Additionally, we compare the following aspects between the control and intervention group: patient transfers; length of inpatient stays; risks, complications and expenses during the inpatient stay; and more frequent clinic presentations. Expenses for patients and the medical staff involved will be included in the analysis (Table 1, last line).

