**Methods:**

To evaluate the complex healthcare intervention “SAFE BIRTH” we will conduct a cluster-randomized controlled stepped-wedge trial in five prenatal medical outpatient offices and eight non-metropolitan hospitals in Saxony, Germany. The offices and hospitals will be randomly allocated to five respectively eight sequential steps over a 30-month period to implement the telemedical IB. We define one specific primary process outcome for each IB (for instance IB#1: “*Proportion of patients with inclusion criterion IB#1 who have a prenatal care plan and psychosocial counseling within one week”*). We estimated a separate multilevel logistic regression model for each primary process outcome using the intervention status as a regressor (control or intervention group). Across all IB, a total of 1,541 and 1,417 pregnant women or newborns need to be included in the intervention and control group, respectively, for a power above 80% for small to medium intervention effects for all five hypothesis tests. Additionally, we will assess job satisfaction and sense of safety of health professionals caring for newborns (questionnaire survey) and we will assess families’ satisfaction, resilience, quality of life and depressive, anxiety and stress symptoms (questionnaire surveys). We will also evaluate the cost-effectiveness of ”SAFE BIRTH” (statutory health insurance routine data, process data) and barriers to its implementation (semi-structured interviews). We use multilevel regression models adjusting for relevant confounders (e.g. socioeconomic status, age, place of residence), as well as descriptive analyses and qualitative content analyses.

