## Discussion

For the HCNSB, the stepped-wedge design offers the advantage of implementing the intervention at the outpatient offices and hospitals at subsequent time points. Compared to classic cluster-randomized studies, the SW-cRCT design offers the advantage that the intervention does not have to be withheld from any participating institution during the study phase. Furthermore, SW-cRCTs prove to be superior to classic cluster-RCTs in terms of power, particularly in the case of a high intra-cluster correlation. However, the design also comes with limitations [18, 19].

Measurement of secondary outcomes via the questionnaire surveys will be across IB and not IB-specific. Qualitative interviews will additionally explore how IB affect the outcomes measured and what barriers to the use of all IB exist on the part of health professionals, pregnant women, and families. They provide supporting information why some individuals benefit more and others less from certain IB and to which individual interventions this is attributable.

Due to the limited project duration, the project is not preceded by a pilot phase. In the start-up phase, adjustments were made to the documentation forms. This was done before the first office and hospital started the intervention phase.

The project started in October 2022. We aim to finish our analyses until spring 2026. Therefore, publication of the results can be expected at the end of 2026 or at the start of 2027.

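### The stated confirmatory model for this stepped-wedge trial names no calendar-time term, so roughly half of any linear background trend would enter the intervention effect

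*Protocol article*

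**What the plan says.** The Data analysis section sets out the confirmatory model in some detail. There is a separate multilevel logistic regression for each of the five primary outcomes, "which contains the intervention status (control or intervention phase) of the respective patient or newborn facility as an explanatory variable". It continues: "The coefficient of this explanatory variable represents the intervention effect". For clustering, "all models contain a random intercept at the institutional level". Tests are two-sided at 5% with a Holm correction over the five hypotheses. The Methods paragraph of the abstract describes the same model: "We estimated a separate multilevel logistic regression model for each primary process outcome using the intervention status as a regressor".

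The only covariates named in the article are in the abstract: "We use multilevel regression models adjusting for relevant confounders (e.g. socioeconomic status, age, place of residence"). None of them is time, and the sentence is not tied to the primary models. The Data analysis section also mentions adjusted regression models for hypothesis 1, without naming a time variable.

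On the design, sites are "randomly allocated to five respectively eight sequential steps over a 30-month period". The section on assignment of interventions says that a case's group follows from when it was included and that the randomised element is the order in which sites cross over. The Discussion says that the design has limitations but does not mention secular trends.

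**The concern.** In a stepped wedge every site moves from control to intervention and none moves back. Within a site, intervention status is therefore a function of calendar time. Randomising the crossover order protects the comparison only if the model contrasts sites in different phases at the same time, and that requires a time term. A random intercept without one pulls the estimate towards within-site contrasts, which are before-after contrasts.

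The primary outcomes are process measures: care plans with counselling, availability of expertise, antibiotic decisions, discharge close to home and psychosocial support. Such measures can drift over 30 months for reasons unrelated to the network. An upward drift would be credited to the intervention, and a downward drift would hide a real benefit. The Background section says that the evaluation will weigh heavily in the reimbursement decision, so bias in either direction matters.

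**Working it through.** **The plan's own figure.** The article states power above 80% with 1,417 control and 1,541 intervention cases over all bundles (2,958 in total). This cannot be reproduced, because target rates, numbers per bundle and the intracluster correlation (ICC) are not given. With an assumed equal split (1,417/5 = 283 and 1,541/5 = 308) and no clustering, a 10-point difference has 69-93% power at alpha 0.05 and 45-80% at alpha 0.01, for control rates of 10-50%. The claim is plausible for some effects but cannot be checked.

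**Inputs from the article.** 8 hospitals in 8 steps, 5 offices in 5 steps, 30 months, two-sided 5%, Holm (smallest p-value against 0.05/5 = 0.01).

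**Assumptions.** Standard wedge with equal-length periods and one site crossing at each step: 8 sites x 9 periods and 5 sites x 6 periods (the allocation figure is not shown). N = 2,958/5 = 592 cases per bundle, equal cells, outcome rate near 50%, ICC 0.01-0.20, linear trend, no true effect.

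**Step 1: time gap.** A site with k of its T periods in control has mean control time (k/2)(30/T) and mean intervention time ((k+T)/2)(30/T). The difference is (T/2)(30/T) = 15 months at every site. Pooled over sites, ignoring site, the gap is 11.1 months (hospitals) or 11.7 months (offices).

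**Step 2: share of the trend absorbed.** For site i the cell means have covariance V = (s²/m)I + τ²J, with s² = 0.25(1 - ICC), τ² = 0.25·ICC and m = N/(sites x periods). The generalised least squares coefficient of intervention status, when the outcome is only a linear trend scaled to 1 over 30 months, is the absorbed fraction f.

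| ICC | f, hospitals | f, offices |
|---|---|---|
| 0.01 | 0.417 | 0.442 |
| 0.05 | 0.467 | 0.481 |
| 0.10 | 0.482 | 0.490 |
| 0.20 | 0.491 | 0.495 |

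So f is 42-50%. It lies between the pooled limit (11.1/30 = 37% or 11.7/30 = 39%) and the within-site limit (15/30 = 50%).

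**Step 3: false positive-direction results.** With a total rise g and standard error SE, the probability is 1 - Φ(z - f·g/SE), where z is 1.96 at 5% and 2.576 at 1%. Worked case, hospitals, ICC 0.05: the effect detectable with 80% power is 12.6 points, so SE = 0.126/2.80 = 0.045.

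- g = 10 points: bias 0.0467, 0.0467/0.045 = 1.04, probability 1 - Φ(0.92) = 18%.
- g = 20 points: bias 0.0934, 0.0934/0.045 = 2.08, probability 1 - Φ(-0.12) = 55%.

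Over all ICC values and both wedges:

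| Rise over 30 months | Two-sided 5% (nominal 2.5%) | First Holm level, 1% (nominal 0.5%) |
|---|---|---|
| 10 points | 16-22% | 5-8% |
| 20 points | 48-67% | 26-43% |

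**Step 4: check on the logistic scale.** A simulation used 500 runs per scenario, baseline 40%, site SD 0.4 on the logit scale, and site fixed effects in place of the random intercept. Without a period term it gave 14-18% with median odds ratio 1.21-1.25 for the 10-point rise, and 53-58% with odds ratio 1.50-1.51 for the 20-point rise. With period effects the rates were 1.6-3.0% and the odds ratios 0.97-1.02, whatever the trend.

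**Step 5: cost of the period effects.** The variance of the intervention effect rises by a factor of 1.9-2.2 (hospitals) or 2.1-2.5 (offices). For an effect with 80% power without period terms, the power kept is Φ(2.80/√ratio - 1.96). At ratio 2.11 this is Φ(1.93 - 1.96) = 49%. The range is 47-53% for hospitals and 43-48% for offices. The effect detectable with 80% power rises from about 12-13 to about 17-19 points.

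**The case against.** The strongest reply is that this is a condensed article. It says that the model contains intervention status, not that it contains nothing else. The abstract's confounder list is open, and an analysis plan that is not shown may include time. That is fair as a caution: the documents do not show that the unseen plan lacks the term. It does not dispose of the point. The article states the fixed effect, the random effect, the coefficient to be read as the effect, the test, the level and the multiplicity rule. A model followed as stated gives a biased effect whenever there is a trend.

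Some stronger readings are tempting but not supported:

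- A reader might infer that the whole secular trend is counted, or that the five tests are pure before-after comparisons. Step 2 shows that about half of a linear trend enters. A random-intercept model also uses some between-site information.
- A reader might infer that a change of data-collection instrument contaminates the contrast, since "In the start-up phase, adjustments were made to the documentation forms". The Discussion places this before any site began the intervention. The project started in October 2022 and the first case was included on 29 January 2023. The article does not say whether any included case was recorded on an old form, so the argument holds only if the forms changed after that first inclusion.
- A reader might take the error rates as predictions. They are not: the documents give no evidence of a background trend of any size. One drift for all bundles is also doubtful, because the limits described for resuscitation expertise and psychosocial staff are structural.

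It also stands that the remedy costs a good deal of power.

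**Conclusion.** The concern holds. As written in the abstract and in the Data analysis section, the confirmatory model has no calendar-time term, and this affects all five primary tests. Under a standard wedge about 42-50% of a linear 30-month trend enters the intervention coefficient, upward or downward. With 592 cases per bundle and no true effect, the false positive-direction rate is about 16-22% for a 10-point rise and 48-67% for a 20-point rise (nominal 2.5%). At the first Holm level it is about 5-8% and 26-43% (nominal 0.5%).

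The mechanism follows from the design and needs no assumption about trend size. The figures depend on the assumed equal split between bundles, equal cells, ICC range and layout. A flat background would produce no bias, but the plan gives no ground for assuming one.

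**What to change.** Add fixed period effects to each primary model and state this in the analysis plan before the confirmatory analysis. If the unseen plan already has them, the published description should say so.

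- **Periods.** Use the office wedge for IB#1 and the hospital wedge for IB#2, #3 and #5. The IB#4 outcome counts newborns cared for at the university hospital, by zip code. Its periods should therefore follow the facility whose phase defines exposure, and the plan should name that facility.
- **Sparse bundles.** For any bundle expected to be sparse, name in advance one lower-order time term, so that its form is not chosen after seeing the data.
- **Few clusters.** Specify a small-cluster correction for 5 or 8 sites. In a separate random-intercept simulation (400 runs per scenario), Wald tests with period effects still rejected in 6-10% of trials at a nominal 5%.
- **Power.** Recompute and restate the claim in the Sample size and recruitment section under this model, with rates, numbers per bundle and ICC.

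No new data are needed. The added terms are eight parameters for a hospital bundle (nine periods) and five for the office bundle (six periods). The real cost is precision: about 1.9-2.5 times the variance, and power of about 43-53% for an effect that would have had 80%.
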